### 2.4. Study Aims

The objective of the study is to evaluate the efficacy of 2 g of MI twice a day for RAIR-TC in inducing the re-uptake of RAI in patients during KI therapy. Although evaluating the effectiveness of the chronic treatment of KIs on re-differentiation is not one of the endpoints of the study, some possible speculations are discussed below.

The primary endpoint is the restoration of 123-I uptake in RAIR-TC patients already on KI therapy alone and on KI therapy plus MI. The restoration of 123-I uptake will be evaluated in target lesions. In the case of multiple lesions, only re-uptake in a target lesion will be considered. A regional target/background ratio of more than 4 and a 2-fold higher iodine uptake than the mean uptake in liver parenchyma according to visual assessment will be considered to indicate responders.

The secondary endpoints are (1) the thyroglobulin trend as a secondary marker of differentiation and (2) the safety and QoL of these patients.

Safety will be assessed according to the clinical symptoms and laboratory parameters. This includes the monitoring of adverse events as defined in the Common Terminology Criteria for Adverse Events (CTCAE) v5.0. All the investigators involved in the study will be responsible for reporting all adverse events occurring during the study.

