## 2. Materials and Methods

### 2.1. Overview of Trial Design

This is an open-label, non-pharmacological, multicenter, randomized pilot study. Data will be collected on RAIR-TC patients being treated with KIs as per clinical practice in multiple institutions across Italy. The protocol was approved by the Ethics Committee (UniCamillus, Rome E00114-2025). The enrollment of patients will start after the protocol’s approval by the ethics committee of each center and will continue until the target sample size has been achieved (see below). The site personnel will capture all the data (epidemiological, clinical, pathological, and biochemical) electronically at the study site in an Excel database provided by the coordinating center.

The MI supplement will be shipped to the hospital pharmacy of the coordinating center and satellite centers. The product will be delivered by the pharmacy to the investigator at each center, who will then dispense it to the patients enrolled in the MI treatment group. The product can be stored at room temperature.

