### 2.2. Eligibility Criteria and Study Design

Patients meeting the eligibility criteria described in Supplementary Table S2 will be included. In summary, RAIR-TC patients will need to have had next-generation sequencing (NGS) analysis for possible mutations. Eligible patients will have a BRAF mutation (treated with sKIs), no mutations, or non-targetable mutations (treated with mKIs). Patients must have been taking KIs for at least four months.

All patients will need to give their written informed consent to be included in the study.

The trial’s design is summarized in Figure 1. Patients will be divided into 2 groups: (1) a control group in which patients are treated with KIs (subgroup a: trametinib plus dabrafenib; subgroup b: lenvatinib); (2) a group (divided into the same subgroups), in which patients are treated with the same KIs in addition to MI. Comparisons will be made between the same subgroups.

MI has a half-life of less than 24 h, and a complete steady state can be achieved in about 4–5 days. However, a longer administration (30 days) helps to ensure an effect on the various metabolic activities. After 30 days of MI treatment, all patients, treated with L-T4 at a semi-suppressive dosage as per clinical practice, will be stimulated with recombinant human TSH (rhTSH) (days 31 and 32). On day 35, patients will be subjected to WBS, with hybrid imaging where possible (SPECT/TC), after the administration of diagnostic activity (185–222 MBq) of 123-I in accordance with the SNMMI/EANM guidelines [28]. Blood samples will be collected before starting MI therapy (day 0); after 30 days of MI therapy; and then on days 31, 32, 33, 34, and 35 after MI therapy. The laboratory assessments are reported in Supplementary Table S3. Quality of life (QoL) will be assessed at the beginning of the MI treatment and at the end of its administration.

Patients will be withdrawn from the study if they experience any side effects from the MI or if they experience adverse unmanageable effects from the KIs, although no known side effects of MI have been reported to date.

The study will be terminated early if there is premature evidence of superiority in the MI group. The study will conclude upon evaluation of the primary endpoint.

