### 2.3. Sample Size and Procedure

We estimate that the difference between the two percentages of subjects in terms of iodine uptake at the end of treatment will equal 30% (for example, 60% in the experimental group and 30% in the control group). We also set the alpha error and power at 5% and 80%, respectively. Given these conditions, 42 patients per group will be necessary for the effect size indicated above to lead to a statistically significant result. A total of 84 patients will therefore need to be enrolled. A chi-square test will be used for the primary endpoint. Univariate and multivariate tests will be used for secondary endpoints. A multivariate logistic regression will be performed adjusting for gender and age.

The patients will be enrolled with a 1:1 ratio in either the control (KI group) or treatment MI (KI plus MI group) groups. The randomization list will be generated using Excel. We will include RAIR-TC patients being treated with KIs as per clinical practice. The enrolled patients will be divided into groups based on the KI type and then into two subgroups: KIs only vs. KIs plus MI. All patients will need to give their written informed consent to be included in the study. If not already available for all patients, an NGS molecular panel will be performed to look for somatic mutations. Each patient will be identified by a two-digit code and patient initials, which are the only identification elements and will only be used for the purposes of the study. Clinical data will be collected during the randomization, on the first (Day 1) and last day (Day 30) of the supplementation with MI (in both the KI and KI plus MI groups), and then on the day of the whole-body scintigraphy (Day 35).

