### 2.5. Data Collection

Demographic data, such as age, gender, race, ethnicity, medical history, TNM stage at initial diagnosis, metastatic disease status, type of metastatic site, and number of organ metastases, will be collected and recorded. Data on TNM, pathological subtype, and somatic molecular mutations will also be collected. History of previous treatments for TC, such as type of surgical treatment, radiotherapy, other KI therapies, or other specific treatments (embolization, chemoembolization, thermal ablation), will be collected. Laboratory data will also be collected on a prespecified day of the study (see Supplementary Table S3).

Data on adverse events will also be collected and recorded according to CTCAE v5.0. The minimum information required is as follows:-Data onset;-The degree of the event’s severity;-Whether the adverse event is serious;-Causality with the drugs;-Any other medical interventions performed by the investigator.

The site personnel will capture all data electronically at the study site in an Excel database provided by the coordinating center.

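### The primary responder rule sets a numeric liver-uptake threshold but has it judged by eye, in an open-label trial

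*Protocol article*

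**What the plan says.** Section 2.4 of the protocol article names restored 123-I uptake in target lesions as the primary endpoint and gives a two-part responder rule. The first part is "A regional target/background ratio of more than 4". The second, joined to it by 'and', is "a 2-fold higher iodine uptake than the mean uptake in liver parenchyma according to visual assessment will be considered to indicate responders". For patients with several lesions, "In the case of multiple lesions, only re-uptake in a target lesion will be considered".

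Three other places bear on how that rule will work:

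- Section 2.1: "This is an open-label, non-pharmacological, multicenter, randomized pilot study".
- Section 2.2, on day 35: "patients will be subjected to WBS, with hybrid imaging where possible (SPECT/TC"). Every patient has the whole-body scan; SPECT/CT is added only in some.
- Section 2.3 compares the responder proportions by chi-square and sizes the trial on an example of "60% in the experimental group and 30% in the control group", giving 42 patients per group.

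The article mentions neither region-of-interest measurement nor any reading arrangement, whether local, central, masked or unmasked.

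**The concern.** Uptake at twice a mean is a quotient of two measured quantities. Assigning that quotient to visual judgement leaves the threshold without a fixed meaning: two readers can classify the same borderline scan differently and both follow the rule. Because both criteria must be met, the visual step can decide the outcome for any patient who passes the first.

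Two things are at stake. If a reader knows the arm and leans, even unconsciously, towards response in the myo-inositol arm, the trial can show a difference that is not there. If reading error is the same in both arms, a true difference shrinks and power falls below the planned 80%. The primary conclusion rests on this one binary call per patient. The article also says that clinical effects will be examined only in a later step, so this trial has no clinical outcome against which to check a misread endpoint.

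**Working it through.** **Inputs from section 2.3:** response 60% versus 30%, alpha 5%, power 80%, 42 per group, 1:1 allocation, chi-square test. Sidedness is not stated; two-sided is assumed because it reproduces the stated size.

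**Inputs assumed, not in the documents:** the reading-error rates, shown as ranges.

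**Step 1. The plan's own figure.** With the pooled-variance formula and no continuity correction,

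n = [1.96 × √(2 × 0.45 × 0.55) + 0.8416 × √(0.6 × 0.4 + 0.3 × 0.7)]² / 0.30²
= (1.379 + 0.565)² / 0.09 = 41.97, so 42 per group.

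The stated size reproduces. Power at 42 per group is 80.0% by the normal approximation. By exact enumeration of the binomial outcomes for the uncorrected chi-square test it is 82.8%. The exact method is used below. Both power figures treat every responder call as correct.

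**Step 2. Arm-dependent reading with no true effect.** The true rate is 30% in both arms. A fraction u of true non-responders in the myo-inositol arm only is called responder, so the observed rate in that arm is 0.30 + 0.70u, against 0.30 in the control arm.

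| u (assumed) | Observed rate, myo-inositol arm | Two-sided rejection |
|---|---|---|
| 0 | 30.0% | 5.1% |
| 5% | 33.5% | 6.5% |
| 10% | 37.0% | 10.7% |
| 15% | 40.5% | 17.9% |
| 20% | 44.0% | 27.9% |

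**Step 3. Equal misreading in both arms with the planned effect.** Observed rate = p × Se + (1 − p) × (1 − Sp).

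- Se = Sp = 0.95: 0.6 × 0.95 + 0.4 × 0.05 = 0.59, and 0.3 × 0.95 + 0.7 × 0.05 = 0.32. Exact power is 74.3%.
- Se = Sp = 0.90: 0.6 × 0.90 + 0.4 × 0.10 = 0.58, and 0.3 × 0.90 + 0.7 × 0.10 = 0.34. Exact power is 64.2%.

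By the normal approximation, against its 80.0% baseline, the same two cases give 71% and 60%.

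**The case against.** **Unmasked site reading.** A reader might infer that scans are read at each site by staff who know the arm. The article does not say so. Open-label describes treatment and does not exclude masked readers. Section 2.5 says "The site personnel will capture all data electronically at the study site in an Excel database provided by the coordinating center", but that concerns data entry, not image reading. An article condenses the full protocol, and reader arrangements are commonly left to it. This part of the objection stands: lack of masking cannot be charged as a stated fault.

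**Both ratios judged by eye.** The visual clause directly follows the liver comparison, and the target/background ratio may well be measured. On that reading, a visual upgrade on the liver criterion cannot rescue a patient who fails the first, which limits how much upgrading is possible. This stands as a limit on size. It does not remove the problem, because the liver criterion is also required.

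**Mixed imaging.** It is tempting to say that one threshold is applied to planar counts in some patients and SPECT counts in others. The article does not say that; hybrid imaging is described as an addition to the whole-body scan. Nor does anything tie SPECT/CT availability to arm. The article simply does not name the acquisition from which the ratios are taken.

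**Illustrative figures.** All error rates are assumed. The mildest case, 6.5%, is only 1.4 points above the 5.1% baseline. The 27.9% case needs one in five true non-responders to be upgraded in one arm only, which nothing in the documents supports.

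**Conclusion.** The concern holds in a narrow form. The published rule makes at least one required part of the sole primary endpoint a numeric threshold decided by visual judgement, in an open-label trial. That rests on what the article states, and a fuller document that measured the ratio would have to depart from the published wording.

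The direction of harm does not depend on the assumed rates: upgrading in the myo-inositol arm alone inflates false positives, and equal misreading costs power. The size does depend on them. Over the ranges tried, the false-positive rate runs from 6.5% to 27.9% against 5.1% without bias, and exact power falls from 83% to 74% or 64%. These figures show how sensitive the test is, not what bias the trial has. The sample-size arithmetic itself is correct.

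Should fix, rather than must fix, because masked reading may exist in the full protocol and the visual clause may cover only the liver criterion.

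**What to change.** In section 2.4:

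1. Delete the reference to visual assessment. State that a responder has a target/background ratio above 4 and a target/mean-liver ratio of at least 2, both computed from region-of-interest counts.
2. Name one acquisition type, available for every patient, from which both ratios are taken. The whole-body scan is the only one that section 2.2 gives to all.
3. State that those who already read the scans score de-identified images without knowledge of arm. If the full protocol already provides this, say so in the article's terms.

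Make the change before any scan is read, since a responder definition revised after unmasked scans have been seen would be hard to defend.

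The cost is some extra measurement on scans that will be acquired anyway, plus removal of identifying labels. If the whole-body scan is chosen, SPECT counts do not enter the primary ratio. A site reader might still recognise a local patient from the images; exchanging scans between centers would reduce that, at some added logistics. No extra scan or patient is needed.

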## 3. Discussion

In this trial, we will evaluate the potential role of the addition of MI to treatment with KIs (sKIs and mKIs) in restoring RAI uptake. From a practical point of view, we decided to investigate the most commonly used drugs: dabrafenib plus trametinib for BRAFV600E mutated cancer and lenvatinib for BRAF wild-type or other non-targetable mutated cancers.

As is well known, RAI uptake is only the first step in the therapeutic effect of RAI. The balance among RAI uptake, iodine organification, and iodine leak or its secretion in thyroid hormones determines the residence time inside the thyroid cells and, hence, the final action of RAI in terms of Gy delivered to the tissue. However, RAI uptake represents the first essential step for RAI treatment.

In our protocol, to simplify the study, we decided to only investigate RAI uptake. From an ethical point of view, we may of course administer RAI therapy in patients in which we find significant RAI uptake in lesions that previously showed no uptake, and subsequently, we will be able to investigate the effects of this treatment. In fact, we decided to evaluate the clinical effects in a second step by imaging after RAI treatment. On the other hand, the Tg values and QoL, as secondary endpoints, are measurable markers of the effects of the treatment.

In the past, various substances and drugs [29,30,31,32] that appeared to increase RAI uptake did not produce clinical effects; however, the robust literature shows that the increase in RAI uptake induced by KIs can have benefits for tumor mass in a percentage of cases.

The novel features of our trial are thus as follows:

Firstly, to the best of our knowledge, this is the first study to explore the possible role of MI in potentiating the re-differentiation of KIs in TC and the potential synergistic effects of MI. Moreover, some studies have shown a potential benefit of MI in oncology, with broad anticancer activity [33,34]. In addition, MI is a nutraceutical agent and virtually free of side effects; this is of special importance for oncological patients. Some studies also suggest improvements in the QoL of patients treated with MI. The double arm in this study will enable us to understand the respective roles of KIs alone and KIs plus MI.

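### The responder rule sets numeric uptake cut-offs but has at least the liver cut-off judged by eye, and the whole primary endpoint depends on that call

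*Protocol article*

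**What the plan says.** Section 2.4 (Study Aims) sets two conditions joined by *and*. It opens with "A regional target/background ratio of more than 4 and a 2-fold higher iodine uptake", and the sentence ends by naming the liver as reference and the eye as instrument: "2-fold higher iodine uptake than the mean uptake in liver parenchyma according to visual assessment will be considered to indicate responders". One lesion per patient counts: "In the case of multiple lesions, only re-uptake in a target lesion will be considered".

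Three other statements bear on how that call is made:

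- Section 2.1 describes the design: "This is an open-label, non-pharmacological, multicenter, randomized pilot study". It also says that the product goes from the pharmacy to the investigator at each center, "who will then dispense it to the patients enrolled in the MI treatment group". Section 2.2 gives the control group kinase inhibitors only, and no placebo is mentioned.
- Section 2.2 schedules the Day 35 imaging: "patients will be subjected to WBS, with hybrid imaging where possible (SPECT/TC". Every patient is therefore due a whole-body scan, but only some will have SPECT/CT.
- Section 2.5 says of the records: "The site personnel will capture all data electronically at the study site in an Excel database provided by the coordinating center".

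The article does not say who reads the scans or whether they know the allocation. It describes no region-of-interest measurement.

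**The concern.** A mean and a 2-fold multiple of it are count quantities. A reader can say that a lesion is brighter than liver, but cannot dependably tell 1.7-fold from 2.2-fold by looking. Section 2.4 therefore states a measured threshold and names a method that does not measure it. This mismatch is in the stated text and does not depend on anything the article leaves out.

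The primary chi-square test rests on this single yes/no result, so reading error matters in two ways:

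- **Error unrelated to arm** moves both observed rates towards each other and shrinks the 30-point difference on which the trial is sized.
- **Error related to arm**, if a reader knew the allocation, would create or hide a difference. A subjective call in an open-label trial is open to this, although nothing in the article shows that it would occur.

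**Working it through.** **Inputs.** Section 2.3 gives responder rates of 60% and 30%, alpha 5%, power 80%, 1:1 allocation, a chi-square test and 42 patients per group. A two-sided test is assumed because it reproduces the stated number. The error rates are assumptions.

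**1. The plan's own figure.** With pooled variance and no continuity correction, p̄ = (0.60 + 0.30)/2 = 0.45 and

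n = [1.96·√(2·0.45·0.55) + 0.842·√(0.60·0.40 + 0.30·0.70)]² / 0.30² = 41.97, rounded up to **42 per group**.

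The stated number is reproduced, so there is no arithmetic error. The calculation assumes error-free classification. Exact binomial enumeration of the uncorrected chi-square test at 42 per arm gives power of 82.8%, against 80.0% by the normal approximation. The exact figures are used below.

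**2. Reading error equal in both arms.** Observed rate = Se·p + (1 − Sp)·(1 − p), where Se is sensitivity and Sp is specificity. For Se = Sp = 0.90:

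- MI arm: 0.90·0.60 + 0.10·0.40 = 0.58
- Control arm: 0.90·0.30 + 0.10·0.70 = 0.34

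| Se | Sp | Observed rates | Difference | Exact power |
|---|---|---|---|---|
| 1.00 | 1.00 | 60% vs 30% | 30 points | 83% |
| 0.95 | 0.95 | 59% vs 32% | 27 points | 74% |
| 0.90 | 1.00 | 54% vs 27% | 27 points | 75% |
| 0.90 | 0.90 | 58% vs 34% | 24 points | 64% |

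The third row covers the case where a measured target/background ratio keeps false positives out and only sensitivity suffers.

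**3. Reading error in the MI arm only, with no true effect.** The true rate is 30% in both arms, and a fraction d of true non-responders in the MI arm is called responder. Observed MI rate = 0.30 + 0.70·d.

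| d | Observed MI rate | Chance of significance favouring MI |
|---|---|---|
| 0 | 30.0% | 2.5% |
| 2% | 31.4% | 3.5% |
| 5% | 33.5% | 5.4% |
| 10% | 37.0% | 10.3% |

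This table shows one direction only. Downgrading in the MI arm, or upgrading in the control arm, would act the other way.

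**The case against.** **The article is silent on masking.** Open-label describes how treatment is given. The investigator who dispenses MI need not be the person who reads the scan, and a full protocol or imaging manual may provide for masked reading. This stands. A reader might infer that scans are read with knowledge of the arm and that the endpoint is biased towards MI. The documents do not support that inference.

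**The visual wording may cover only the liver criterion.** By position it attaches to the liver clause, and the ratio above 4 may be measured. This also stands, and it could limit false positives. It does not remove the problem, because the two conditions are joined by *and*, so every responder must still pass the visual one.

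**The prospect of radioiodine therapy gives no direction.** Section 3 says "we may of course administer RAI therapy in patients in which we find significant RAI uptake". It is tempting to see here a motive to favour MI, but the statement applies to both arms. By itself it could raise both response rates and gives no reason to expect a difference between them.

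**The damage may be reversible.** If the Day 35 images are kept, they can be re-measured later. This is fair, and nothing in the article says that only the visual call is stored. A later re-measurement would, however, be a post hoc change to the primary endpoint.

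**The magnitudes are assumed.** This is correct, and milder error has smaller effects, which is why the tables include the mild cases.

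**Conclusion.** The point holds as a defect in how the primary endpoint is measured. Section 2.4 ties a count-based cut-off to a visual method that cannot reliably establish it, and the primary result depends on that step whichever way the sentence is parsed.

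The cost in power is 8 to 19 percentage points (82.8% to between 74.3% and 64.2%) for the assumed error rates in the first table. The exposure to arm-related bias is a possibility only. The increase in false-positive findings from 2.5% to between 3.5% and 10.3% shows what small amounts of arm-related reading would do if it occurred in that direction. Neither set of figures estimates what will happen in this trial. The planned sample size is correct for its stated assumptions and need not change.

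**What to change.** In Section 2.4, replace the reference to visual assessment with a measurement:

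- On the Day 35 images already scheduled, draw regions of interest on the target lesion, on a background region that the protocol names, and on the liver. Section 2.4 does not at present say which background is meant.
- Compute both ratios from mean counts. Use the same image type for all patients, for example the whole-body scan that every patient is due to have, so that planar and SPECT values are not mixed.
- Apply the existing cut-offs to the computed values, and record the ratios themselves as well as the yes/no result.
- Keep the visual call as a sensitivity analysis.
- Have whoever already reads the scans make the measurements on files coded without the arm, where this needs no added reader. If the full protocol already provides masked reading, it is enough to say so here.

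The cost is protocol wording, a few minutes of region drawing per scan, and file coding. No extra scan or patient is needed, and the sample size stays at 42 per group.
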